## Background

### Epicardial adipose tissue and coronary atherosclerosis

Epicardial adipose tissue (EAT) is directly deposited around the pericardium and coronary artery. By autocrine and paracrine means, EAT can generate various kinds of cytokines, inflammatory mediators and free fatty acids. These biological indicators can affect the state of coronary endothelial function and promote inflammation and oxidative stress, which finally aggravate the progression of coronary atherosclerosis [1–3]. A significant amount of clinical research has been conducted to investigate the link between EAT and coronary atherosclerosis. It was claimed that calcified plaque progression in patients without coronary artery disease and in patients with type 2 diabetes mellitus were associated with a larger EAT volume [4, 5]. Epicardial adipose tissue is also an independent predictor of significant coronary stenosis and is independently associated with high-risk coronary plaque features, such as low CT attenuation plaque, thin-cap fibroatheroma and positive remodeling [6]. Not only is EAT, as a special visceral fat, correlated with the increased development of coronary artery atherosclerosis, but it is also associated with adverse coronary events [7].

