#### Aims of the anti-atherosclerosis mechanism study

To explore the relationship between coronary atherosclerosis progression and EAT volume reduction.To explore the effect of olmesartan medoxomil on serum levels of blood lipids, glucose, circulating surrogate markers of atherosclerosis inflammation, including high-sensitivity C-reactive protein, IL-6, monocyte chemotactic protein 1 (MCP-1), TNF-α, and matrix metalloproteinase 9 (MMP-9), circulating surrogate markers of endothelial function, including NO and endothelin 1 (ET-1), and circulating surrogate markers of adipose tissue inflammation and metabolism, including adiponectin and leptin at baseline and after 6 and 12 months.

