#### Epicardial adipose tissue quantification

The EAT volume will be measured by two experienced radiologists using the same sets of images acquired for the CCTA. The radiologists will be blinded to the purpose of the study, clinical characteristics and patients’ anthropometric data.

The EAT volume is defined as the total amount of adipose tissue deposited between the surface of the heart and the visceral pericardium. The region of interest in measuring the EAT volume includes the heart and the surrounding EAT. By manually tracing the epicardium contours in the axial slices from the bifurcation of the pulmonary artery to the diaphragm, the EAT volume is analyzed. The pericardium contour is traced every 10 mm, from the lower visible level of the pulmonary artery bifurcation until the top level of the pulmonary valve, for every 20 mm until the first slice where the diaphragm becomes visible, and for every 10 mm from this point until the last slice where the pericardium is still visible [31]. The pericardium contour is manually outlined by the radiologists, and then the software (Syngo Volume, Siemens Medical Solutions) automatically calculates the total EAT volume. Computed tomography attenuation ranging from −195 to 45 Hounsfield units is applied to isolate the EAT from other tissues. Mediastinal adipose tissue and pericardial adipose fat (fat deposit outside the visceral pericardium and on the external surface of the parietal pericardium) are excluded from the analysis. For the assessment of interobserver agreement, we will randomly select 50 patients, and all EAT measures will be assessed by two experienced radiologists blinded to the other radiologist’s measurements.

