### Study outcomes

The primary outcome measures are coronary atherosclerosis progression and EAT volume changes, as detected by CCTA at 12 months.

The secondary outcome measures includeThe relationship between coronary atherosclerosis and EAT;Serum levels of blood lipids, glucose, circulating surrogate markers of atherosclerotic inflammation including high-sensitivity C-reactive protein, IL-6, MCP-1, TNF-α, and MMP-9, individual circulating surrogate markers of endothelial function including NO and ET-1, and individual circulating surrogate markers of adipose tissue inflammation and metabolism including adiponectin and leptin at baseline and after 6 and 12 months.

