### Sample size calculation

This trial is an open-label randomized clinical trial, so patients will randomly be assigned to olmesartan medoxomil or conventional antihypertensive medication groups (1:1 ratio). The purpose of this study is to verify that olmesartan medoxomil is effective in the treatment of coronary atherosclerosis progression and EAT volume reduction in patients with coronary atherosclerosis detected by CCTA. We also want to elucidate the relationship between coronary atherosclerosis and EAT. The mechanism by which olmesartan medoxomil inhibits coronary atherosclerosis progression will be studied by detecting the serum levels of blood lipids, glucose, circulating surrogate markers of atherosclerosis inflammation including high-sensitivity C-reactive protein, IL-6, MCP-1, TNF-α, and MMP-9, circulating surrogate markers of endothelial function, including NO and ET-1, and circulating surrogate markers of adipose tissue inflammation and metabolism, including adiponectin and leptin.

Studies on coronary atherosclerosis progression rate have had differing results. The combined results of multiple studies indicate that the conventional mean coronary atherosclerosis progression rate is about 30 % [33–35]. We hypothesize that additional olmesartan medoxomil use will reduce the coronary atherosclerosis progression rate to 13 % [36–40]. Using double-side inspection, α = 0.05, β = 0.2, we calculate a total sample size of 176 cases; considering the expected loss to follow-up to be 10 %, the number of cases to be included should be at least 176 × (1 + 10 %) = 194. Therefore, we aim for 97 cases of each group.

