### Statistical analysis

Continuous variables will be described using means and standard deviations or median and range in case of asymmetric distribution of data. Categorical variables will be presented using frequency distribution. Univariate analyses will be conducted using chi-square and *t* tests for independent samples. A multiple logistic regression analysis will be performed to correlate coronary atherosclerosis progression with clinical variables and EAT volume, including treatment groups. Statistical significance will be considered for *P* < 0.05. A statistical package (SPSS 16.0) will be used for analysis. The individual will be considered the unit of analysis.

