## Discussion

To date, there are ample CCTA studies exploring the progression of coronary atherosclerosis following pharmacological manipulation. As studies show that EAT volume is associated with plaque progression and cardiovascular adverse events, treatments aimed at reducing EAT volume may finally achieve an antiatherosclerotic, preventive effect. However, at the time of writing, only a limited number of studies have aimed to reduce both EAT and plaque volume to achieve a preventive effect against atherosclerosis. The novelty of this study is that we intend to explore the effect of olmesartan medoxomil on both plaque volume and epicardial fat. This study will accomplish two goals: (1) it will explain the relationship between EAT volume and coronary atherosclerosis progression and (2) it will verify the effect of olmesartan medoxomil on EAT volume reduction and coronary atherosclerosis progression.

If these hypotheses are supported, the study findings will have significant implications related to clinical practice. Evidence that olmesartan medoxomil is effective on EAT volume reduction and coronary atherosclerosis progression would be very attractive to clinicians and patients. This may further contribute to the care of patients with coronary heart disease.

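### One aim concerns EAT volume reduction, but the only model linking EAT to progression enters EAT volume as a level with no time point; enter the change together with baseline

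*Protocol article*

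**What the plan says.** All references are to the protocol article.

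- Aims of the anti-atherosclerosis mechanism study, first aim: "To explore the relationship between coronary atherosclerosis progression and EAT volume reduction". This is a question about change.
- Statistical analysis gives one model relating progression to EAT: "A multiple logistic regression analysis will be performed to correlate coronary atherosclerosis progression with clinical variables and EAT volume, including treatment groups". It names no scan time and no change term.
- Epicardial adipose tissue quantification: "The EAT volume is defined as the total amount of adipose tissue deposited between the surface of the heart and the visceral pericardium". This is a level.
- Study outcomes words change separately when change is meant: "The primary outcome measures are coronary atherosclerosis progression and EAT volume changes, as detected by CCTA at 12 months".
- Elsewhere the goal is looser. Sample size calculation speaks of "the relationship between coronary atherosclerosis and EAT", the secondary outcome list does much the same, and goal (1) of the Discussion is that "it will explain the relationship between EAT volume and coronary atherosclerosis progression".
- The Background reports a level association from other studies: "calcified plaque progression in patients without coronary artery disease and in patients with type 2 diabetes mellitus were associated with a larger EAT volume".

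**The concern.** How much EAT a patient has and how much of it is lost over a year are different quantities. The coefficient of a level asks whether patients with larger EAT progress more. The mechanism aim asks whether patients whose EAT shrinks progress less.

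The article's rationale rests on the second question. It argues that lowering EAT may protect against atherosclerosis, and it faults a serial CCTA study of intensive statin therapy for not tying EAT reduction to progression. A level coefficient leaves that gap open. At stake is a significant EAT term being presented as support for the reduction hypothesis when it is not, or a null EAT term being taken as evidence against a relation that the model could hardly detect.

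**Working it through.** **1. The plan's own figure.** For 30 % v 13 %, two-sided α = 0.05 and 80 % power, with unpooled variance: n per arm = (1.960 + 0.842)² × (0.30×0.70 + 0.13×0.87) / 0.17² = 7.849 × 0.3231 / 0.0289 = 87.75, so 88 per arm and 176 in total. The stated 176 reproduces. It does not bear on this point, except that it fixes the expected number of progressors: 88×0.30 + 88×0.13 = 26.4 + 11.4 ≈ 38.

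**2. Why a level is a poor stand-in for change.** The 12-month level is baseline plus change. If the two parts are uncorrelated within arm, the correlation of the 12-month level with change is SD(change) / √(SD(baseline)² + SD(change)²). The document gives neither SD. Assume 40 ml for baseline and 10 or 20 ml for change:

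- 10 / √(1600 + 100) = 0.24
- 20 / √(1600 + 400) = 0.45

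The matching correlations with baseline are 40/41.2 = 0.97 and 40/44.7 = 0.89. Under these assumptions the 12-month level mostly carries baseline, and a baseline level carries no information on change.

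**3. Illustrative simulation.** From the document: n = 176, equal arms, P < 0.05, with intercept and treatment effect set to the 30 % and 13 % planning rates, and treatment in the model. Assumed: the SDs above, a mean treatment effect on EAT of −5 ml, and an odds ratio of 1.8 per SD for whichever EAT quantity is active. There were 2,000 runs per cell. Share of runs in which the EAT term is significant:

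| What drives progression | EAT term in the model | SD of change 10 ml | SD of change 20 ml |
|---|---|---|---|
| Level only | baseline level | 86 % | 85 % |
| Level only | 12-month level | 83 % | 77 % |
| Level only | change, with baseline | 6 % | 4 % |
| Change only | baseline level | 5 % | 4 % |
| Change only | 12-month level | 11 % | 26 % |
| Change only | change, with baseline | 85 % | 86 % |
| Neither | any of the three | 4–6 % | 4 % |

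**4. Range over other assumptions** (n = 175, SD of change 0.1 to 0.5 of the baseline SD if change matters and 0.2 to 0.5 if only the level does).

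- Level only, odds ratios 1.5, 1.75 and 2.0 per SD: the baseline term is significant in about 55 %, 82 % and 95 % of runs, the 12-month term in 46–54 %, 75–82 % and 88–94 %, and change with baseline in 4–6 % throughout.
- Change only, odds ratio 1.75 per SD: the baseline term is significant in 5 % of runs. The 12-month term reaches 6 %, 8 %, 11 % and 25 % at SD ratios 0.1, 0.2, 0.3 and 0.5, and change with baseline 82–84 %.

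**5. Why baseline must accompany change.** In the step 3 set-up, if change correlates −0.3 with baseline and only the level matters, change alone is significant in 14–15 % of runs. With baseline in the model it is about 5 %.

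**The case against.** The case on the other side has real weight.

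- **Most statements of the goal omit reduction.** Only the mechanism aim uses the word in this sense, and goal (1) of the Discussion matches the model. This stands: the model does not contradict every statement of the objective. It fails to answer one of them, and the sections need aligning.
- **The model sentence is a summary.** Without a scan time, the authors may have meant change. That is possible. Even so, the article defines EAT volume as an amount and says changes or reduction when it means those, so an analyst following the text would enter a level. The point concerns a stated covariate, not a detail left to an unseen plan.
- **No null hypothesis is stated.** The aim is to explore a relationship, and no error rate is attached to it. This stands. The simulated percentages show how often each term would reach the general P < 0.05 criterion; they are not breaches of a promised error rate.
- **The Background association.** A reader might infer that the level association is already established, so that the EAT term is bound to be positive. The text does not support this. It concerns calcified plaque progression in patients without coronary disease and in type 2 diabetes, whereas this trial enrols hypertensive patients with 30–70 % stenosis and defines progression by stenosis or minimal lumen diameter. The association makes a level effect plausible, no more.
- **The scenarios are stylised.** Level-only and change-only cannot both describe this trial, and the simulated models leave out the clinical variables that the plan would include. This stands too.

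**Conclusion.** The mismatch is real and worth correcting. Under either scan time, the covariate as written does not answer the aim about EAT reduction. The simulations show that the error can run in both directions: a significant level term with no role for change, and a weak or absent signal when change does matter. Their sizes depend on assumed odds ratios and SD ratios that the document does not give, and should not be quoted as error rates or power of this trial.

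A reader might also infer that the trial's main conclusions are at risk. They are not. The aim is secondary and exploratory, and the between-arm comparisons of the two primary outcomes and N = 176 do not depend on this model. Nor would the corrected model show that shrinking EAT slows progression: EAT change arises after randomisation and is measured at the same 12-month scan as progression, so the result is an association.

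**What to change.** In Statistical analysis, for the mechanism aim, replace EAT volume in the logistic model with two terms, the change in EAT volume from baseline to 12 months and the baseline EAT volume, and keep treatment group. State that the change coefficient answers the aim, report the baseline coefficient separately as the level association, and describe both as associations.

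Use the same wording for this goal in the mechanism aims, Study outcomes, Sample size calculation, Statistical analysis and Discussion.

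No new data are needed, because the primary outcome of EAT volume changes already requires both measurements. The cost is one more degree of freedom against about 38 expected progressors, so one fewer clinical covariate may be affordable.

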## Discussion

To date, there are ample CCTA studies exploring the progression of coronary atherosclerosis following pharmacological manipulation. As studies show that EAT volume is associated with plaque progression and cardiovascular adverse events, treatments aimed at reducing EAT volume may finally achieve an antiatherosclerotic, preventive effect. However, at the time of writing, only a limited number of studies have aimed to reduce both EAT and plaque volume to achieve a preventive effect against atherosclerosis. The novelty of this study is that we intend to explore the effect of olmesartan medoxomil on both plaque volume and epicardial fat. This study will accomplish two goals: (1) it will explain the relationship between EAT volume and coronary atherosclerosis progression and (2) it will verify the effect of olmesartan medoxomil on EAT volume reduction and coronary atherosclerosis progression.

If these hypotheses are supported, the study findings will have significant implications related to clinical practice. Evidence that olmesartan medoxomil is effective on EAT volume reduction and coronary atherosclerosis progression would be very attractive to clinicians and patients. This may further contribute to the care of patients with coronary heart disease.

## Trial status

Recruitment for the study is currently ongoing. Patient recruitment began in December 2014.

## Abbreviations

CCTA: coronary computed tomography angiography
CT: computed tomography
CYP450: cytochrome P450
EAT: epicardial adipose tissue
ET-1: endothelin 1
IL-6: interleukin 6
MCP-1: monocyte chemotactic protein 1
MMP-9: matrix metalloproteinase 9
TNF-α: tumor necrosis factor α
